## Abstract

**Background:**

Vaccination is one of the most effective strategies for prevention and eradication of immunopreventable diseases, but community acceptance of vaccination can be influenced by different factors, such as pain and anxiety. The use of high-frequency vibration associated with cryotherapy has been used to manage pain and anxiety during the vaccination process in children, but studies with adults are still scarce. This study aims to evaluate the effect of high-frequency vibration associated with cryotherapy on the levels of self-reported pain and anxiety related to administration of the Influenza vaccine intramuscularly in adults.

**Methods:**

A two-arm, parallel, randomized clinical trial conducted in a Brazilian Primary Health Care Unit is proposed. A sample of 350 adults will be randomly assigned to participate in the control group, receiving the vaccine intramuscularly according to the standard protocol of the service, or in the intervention group, receiving the vaccine by the same route and using a portable device of high frequency vibration associated with cryotherapy for 30 s before and during administration. The primary endpoints will be self-reported levels of pain, assessed before and after vaccine administration. Secondary endpoints will be levels of anxiety, satisfaction with vaccine administration, and discomfort caused by high frequency vibration and temperature of the frozen bag in contact with the skin. Self-reported levels of pain and anxiety will be compared before and after vaccination as well as between the control and intervention groups.

**Discussion:**

By evaluating the effect of high-frequency vibration associated with cryotherapy on pain and anxiety levels, we expect to find evidence that will support nursing practice, in order to promote greater comfort and safety in the vaccination process and, consequently, greater compliance by the population, by minimizing its undesirable effects.

**Trial registration:**

Human Research Ethics Committee Opinion Number: 5.138.564. Approved on December 2, 2021. Brazilian Registry of Clinical Trials (REBEC): Registration number RBR-5zgy25w. Registered on December 09, 2021.

**Supplementary Information:**

The online version contains supplementary material available at 10.1186/s13063-022-06564-7.

## Administrative information

Note: the numbers in curly brackets in this protocol refer to SPIRIT checklist item numbers. The order of the items has been modified to group similar items (see http://www.equator-network.org/reporting-guidelines/spirit-2013-statement-defining-standard-protocol-items-for-clinical-trials/).

## Introduction

### Background and rationale {6a}

Influenza is an acute viral infection that affects the respiratory system [1, 2]. The severity and impact of the disease are associated with the virulence and the degree of transmissibility of the virus, as well as the adherence to preventive measures by the community [3].

It is estimated that each year, 20% of the world’s population is infected, with severe Influenza infection being one of the leading causes of morbidity and mortality worldwide [4]. The largest pandemic historically recorded occurred in 1918 and was caused by the influenza A H1N1 virus, known as the Spanish flu, responsible for more than 20 million deaths worldwide [5]. In 2009, again the influenza A virus caused the first pandemic of the twenty-first century, with mortality of almost 400,000 individuals [3].

Among the measures of prevention and control, the annual vaccination against influenza virus, adopted by several countries [3, 6], stands out. In Brazil, the National Immunization Program annually coordinates the national vaccination campaign since 1999 [7]. However, despite the importance of vaccination, it is found that in different countries, the campaign against Influenza has low adherence. In 2017, in Spain, only 40.3% of the population with chronic conditions received the immunization [8]. Similarly, in 2021, in China, only 4.7% of the elderly aged 60 years and older were vaccinated [9]. In the national context, vaccination coverage has been advancing from 70% in 1999 to 82.8% in 2020 [10]. However, despite the positive increase in the vaccinated population, 50,482 cases of Influenza infection were confirmed in 2009 [5] and 2.150 in 2020 [10].

The causes for people’s non-vaccination or hesitation are complex and diverse issues, as they involve social, cultural, and economic aspects and may vary from one place to another [11]. Among the main causes are misinformation (73.9%) [12, 13], fear of the needle, and adverse events (55.4%) [14].

The fear of the needle is a result of the pain generated during application in the muscle, being considered a personal and subjective experience. This individual perception can be influenced, in variable degrees, by biological, psychological, and social factors, with consequent anxiety in future immunizations [15].

Vaccine-related pain and anxiety have gained prominence on the international scene. In 2015, the World Health Organization (WHO) issued a position paper on this issue and presented a variety of feasible evidence-based, mostly non-pharmacological, accessible, easy to perform, low or no cost, training- and time-intensive interventions, such as tactile stimulation, distraction, high-frequency vibration, and cryotherapy (ice pack) [16].

The use of high-frequency vibration associated with cryotherapy as a non-pharmacological strategy for the relief of pain related to needle procedures has been used, especially in the pediatric population [17–20]. A randomized clinical trial (RCT) demonstrated that during vaccination, the group of children who received high-frequency vibration associated with cryotherapy had lower mean reported pain scores than children who did not receive this intervention (3.56 vs 5.92—*p* = 015,0) [21]. In adults, two international studies demonstrated the effectiveness of the portable high-frequency vibration device associated with cryotherapy on pain and anxiety levels during intramuscular (IM) vaccine administration [22]. However, there is a lack of national studies aimed at evaluating the effect of this intervention in the general adult population.

Thus, controlled clinical trials of high methodological quality are necessary to evaluate the effect of non-pharmacological nursing interventions such as high-frequency vibration associated with cryotherapy on the levels of self-reported pain and anxiety related to the administration of influenza vaccine by IM in adults. The results of this study may support the reorientation of nursing practices in order to promote greater comfort for the population and safety in the vaccination process. Thus, it is expected to improve the adherence of adults to immunization campaigns by minimizing undesirable effects during administration, especially pain.

### Objectives {7}

The general objective of this study is to evaluate the effect of high frequency vibration associated with cryotherapy on the levels of self-reported pain and anxiety related to the administration of the Influenza vaccine by IM in adults. In addition, it has as secondary objectives:To evaluate the level of self-reported pain expected by adults before administration of the Influenza vaccine by IM with and without the use of high-frequency vibration associated with cryotherapyTo evaluate the level of pain self-reported by adults after administration of the Influenza vaccine by IM with and without the use of high-frequency vibration associated with cryotherapyTo evaluate the level of anxiety self-reported by adults before and after administration of the Influenza vaccine by IM with and without the use of high-frequency vibration associated with cryotherapy

### Trial design {8}

This is a parallel, open, two-armed RCT, with allocation of participants in a 1:1 ratio and structured to evaluate the superiority of the use of a portable high-frequency vibration device associated with cryotherapy, on the levels of pain and anxiety related to the administration of the influenza vaccine (intervention group—IG), compared to the absence of its use (control group—CG).

## Methods: participants, interventions, and outcomes

### Study setting {9}

The study will be conducted in a vaccination room of a Basic Health Unit located on the premises of a public Brazilian higher education institution. This is a service that offers multidisciplinary outpatient care with doctors, nutritionists, nurses, dentists and speech therapists, directed to students, teachers, and technical-administrative servers of that institution.

The vaccination room is accredited with the Brasilian Ministry of Health and open to the entire community. The team of professionals working in vaccination consists of a nurse, a nursing technician and a nursing assistant. The national immunization program provides nineteen vaccines for different age groups, among them the influenza, in addition to special immunobiologicals, sent to patients with contraindications for the vaccines usually administered or patients in special conditions of morbidity.

### Eligibility criteria {10}

The study population will consist of adults who come to the basic health unit to receive the influenza vaccine by the IM route during the National Immunization Campaign of the year 2022.

Participants will be included if they are 18 years of age or older, have good cognition, are literate, and exclusively receive influenza vaccine via IM in the deltoid region during the study.

Participants with previous reports of pain in the upper limbs, presence of lesions or abrasions in the deltoid region, loss or alteration of sensation in the upper limbs, and previous use of analgesics in the last six hours prior to immunization will be excluded.

### Who will take informed consent? {26a}

All potential participants will be invited to participate in the study by personal contact made by members of the study team while waiting to receive the vaccine. The researchers will explain the details of the study to the potential participants, and if they are interested in participating, they will be asked to read and sign the informed consent form.

### Additional consent provisions for collection and use of participant data and biological specimens {26b}

Not applicable. The study does not include biological data collection.

## Interventions

### Explanation for the choice of comparators {6b}

The control group (CG) will be composed of participants who received the vaccine intramuscularly, according to the standard protocol of the service, without the use of any intervention for pain relief and anxiety. This group will be compared with the intervention group (IG).

### Intervention description {11a}

Patients will be randomized and assigned to one of two groups: control group (CG) or intervention group (IG). They will remain in these groups until the end of the study.CG: participants who will receive the influenza vaccine by IM as per the standard protocol of the service, without the use of any intervention for pain relief and anxietyIG: participants who will receive the influenza vaccine by IM route using the portable high-frequency vibration device associated with cryotherapy for 30 s before application and during administration of the vaccine. The reusable plastic handheld device called Buzzy® has a reusable ice pack (cryotherapy) and a button to trigger the high-frequency vibration. The device is based on the pain gate control theory by using the non-painful stimuli of cold and high frequency vibration on the deltoid before and during vaccine administration to inhibit the transmission of painful stimuli [19]

The research will take place during the 2022 National Influenza Immunization Campaign, starting in April. The principal investigator will be responsible for administering the influenza vaccine to all participants in both groups.

The influenza vaccine consists of inactivated, fractionated, and purified viruses, characteristics that ensure that it does not cause the disease. The immunobiological distributed free of charge by the Ministry of Health will be used. The influenza vaccine (fragmented, inactivated) is an injectable suspension composed of different strains of the inactivated, fragmented, and purified Myxovirus influenzae virus, A/Victoria/2570/2019 (H1N1)pdm09; A/Darwin/9/2021 (H3N2); B/Austria/02/1359417/2021 (linhagem B/Victoria).

In both groups (control and intervention), the participants will be seated, in an air-conditioned environment, and will receive guidance about the procedure and possible adverse events. If there is no contraindication, the participants can choose which limb they want to receive the vaccine in (right or left deltoid). The researcher will perform hand hygiene and help with the correct positioning, keeping the forearm of the selected limb over the abdomen, with the aim of relaxing the shoulder.

CG: The researcher will check the integrity of the immunization liquid and expiration date of the vial with the participant. The researcher will clean the rubber of the vial with dry cotton and will attach a 25 × 7.0 dec/mm needle to the 1 ml sterile syringe and insert it into the vial. He will homogenize the liquid and then aspirate 0.5 ml of immunizer, as directed by the Health Ministry. After aspiration of the immunizing liquid, the needle will be replaced by the 25 mm × 0.6 dec/mm needle. The 25mm × 0.6dec/mm needle, attached to the syringe, will be inserted completely into the deltoid muscle at a 90° angle to the skin of the arm, then the vaccine will be administered quickly to reduce the time the needle stays in the muscle. The needle will be removed at a 90° angle, while the researcher with a cotton swab, lightly presses the muscle. After complete removal of the needle, compression will be maintained on the application site, without massage, for approximately 30 s. After this time, the presence of local reactions, such as bleeding, will be evaluated. If present, compression will be maintained until the bleeding stops completely and an antiseptic bandage will be applied.

IG: The researcher will check the integrity of the immunizer liquid and expiration date of the vial with the participant. The researcher will clean the rubber of the vial with dry cotton and will attach a 25 × 7.0 dec/mm needle to the 1 ml sterile syringe and insert it into the vial. He will homogenize the liquid and then aspirate 0.5 ml of immunizer, as directed by the Health Ministry. After aspiration of the immunizing liquid, the needle will be replaced by a 2 5mm × 0.6 dec/mm needle. An assistant researcher will remove the ice pack (cryotherapy) from the freezer at the moment of vaccine administration and will attach it to the portable vibration device. The button to trigger the vibration will be turned on, the device will be attached to the site where the vaccine will be administered (deltoid muscle) and will remain for 30 s. The device’s dwell time will be timed, using a Vollo® digital stopwatch with alarm. After this time, the attached device will be slid about 2 cm above the administration site and the vaccine will be administered by the principal investigator. The 25 mm × 0.6dec/mm needle, attached to the syringe, will be inserted fully into the deltoid muscle at a 90° angle to the skin of the arm, and then the vaccine will be administered quickly to reduce the time the needle remains in the muscle. The needle will be removed at a 90° angle while the researcher lightly presses the muscle with a cotton swab. After complete removal of the needle, compression will be maintained at the application site, without massage, for approximately 30 s. The handheld device will be turned off and removed from the limb. Local reactions such as bleeding will be evaluated. If present, compression will be maintained until the bleeding stops completely, and an antiseptic bandage will be applied. The assistant researcher will disinfect the portable high-frequency vibration device and the ice pack with 70% alcohol. The ice pack will be returned to the freezer for later use.

After vaccine administration, the syringe and needle packaging will be discarded in regular trash containers and the vaccine bottle in an appropriate place, according to legislation. The researcher will perform hand hygiene and sign the full name legibly on the vaccine card and return it to the participant, who will be instructed to remain on the premises for 15 minutes to observe for possible adverse events.

### Criteria for discontinuing or modifying allocated interventions {11b}

Vaccination is a one-time intervention, and assessment of outcomes will occur before and after administration. However, during its realization, the volunteer may be discontinued if he/she withdraws from the study. For the participants of IG, the discontinuation may occur by any change or discomfort related to the use of the portable vibration device associated with cryotherapy.

It should be noted that participants who withdraw from the study will be guaranteed the right to be immunized and the health professional will perform the procedure according to the standard protocol of the service and the guidelines of the Ministry of Health. If the participant has contraindications to receive the vaccine in both deltoids, the vaccine may be administered in the ventro gluteal muscle; however, participants who receive the vaccine by this route will not be included in the study.

### Strategies to improve adherence to interventions {11c}

Since this is a one-time intervention, participants will not be required to complete any follow-up time, which facilitates adherence. All participants’ questions about the procedure will be answered at any time during the research. In IG participants, the dwell time of the handheld device on the deltoid prior to vaccine administration will be timed for 30 seconds, so as not to exceed the required time and cause any discomfort that may influence the participants’ acceptance.

### Relevant concomitant care permitted or prohibited during the trial {11d}

Participants having used analgesics in the last six hours prior to vaccination will not be included in the study, in order to avoid influencing the primary outcome—pain.

A companion will be allowed to be present during the administration of the vaccine, if the participant wishes.

### Provisions for post-trial care {30}

The participant will be evaluated in relation to his/her state of anxiety. Thus, if he/she develops any psychological discomfort/shock as a result of the research, he/she will be referred for psychological treatment with a Psychologist Specialist in Cognitive-Behavioral Therapy, at no cost to the participant.

The influenza vaccine, as well as other vaccines, may cause adverse events; if the participant presents any of them, he/she will be referred to a physician specialized in Infectious Diseases and Allergies, at no cost for the participant. In case of severe reactions immediately after the vaccination, the participant will be attended by the health unit staff and, if necessary, the Mobile Emergency Care Service will be requested.

If the participant presents any adverse event at home, he/she must contact the responsible researcher by phone, who will make the referrals and schedule an appointment with the psychologist or doctor of the research team.

In the face of eventual damages, identified and proven, resulting from the research, the participant is assured the right to compensation.

All adverse events will be described, analyzed, and reported.

### Outcomes {12}

#### Primary outcomes

The primary outcome is pain, collected in two instances: before and after vaccination. The primary outcome will be compared between groups (control and intervention), by Student’s *t* test or Mann-Whitney test, and also within groups (before and after vaccine administration) by paired Student’s *t* test or Wilcoxon test, according to the result of normality test.Pain: Numerical variable, measured before and after vaccine administration. Data collected from the numerical pain scale, from 0 to 10, being classified as 0 equal to no pain; 1–4 mild pain; 5–6 moderate pain; 7–9 severe pain; and 10 worst pain [23].

#### Secondary outcomes

Anxiety: Numerical variable, measured before and after vaccine administration, from the visual analog anxiety scale, in which they should mark their anxiety level along a horizontal line with a scale of 0–10 (0 = no anxiety and 10 = highest possible anxiety) [22, 24].Satisfaction with vaccine administration: ordinal variable, measured on a 10-point Likert scale (0 = totally dissatisfied; 10 highest possible satisfaction) [22];Discomfort caused by the temperature of the frozen bag in contact with the skin: rated only by the IG participants, by a Likert scale (0 = “not at all” to 10 = “extremely uncomfortable” [22];Discomfort caused by the vibration of the device in contact with the skin: rated only by the IG participants, by a Likert scale (0 = “not at all” to 10 = “extremely uncomfortable”) [22].

### Participant timeline {13}

The steps of the study will be conducted based on the Consolidated Standards of Reporting Trials (CONSORT) guidelines for reporting clinical trials in a clear, transparent, and comprehensive manner [25]. The protocol is reported according to the Standard Protocol Items: Recommendations for Intervention Trials (SPIRIT) statement [26]. Table 1 presents the operationalization steps of the study.

**Table 1 Tab1:** Stages of study operationalization 2022

Steps	Study period			
	Enrolment	Allocation	Intervention	Post-intervention
**Timepoint:**	-T_1_	T_0_		T_1_
**Enrolment:**				
Identification of the Study Population - National Influenza Immunization Campaign	X			
Eligibility Criteria	X			
Informed Consent	X			
**Randomisation**				
Allocation of participants		X		
**Interventions**				
Control Group			X	
Intervention Group			X	
**Assessment**				
Sociodemographic Data Collection	X			
Expected level of pain with the vaccine	X			
Self-reported anxiety level before the vaccine	X			
Level of self-reported pain after vaccination	X			X
Self-reported anxiety level after the vaccine				X
Satisfaction with vaccine administration				X
Discomfort caused by the temperature of the frozen bag in contact with the skin				X
Discomfort caused by the vibration of the device in contact with the skin				X

### Sample size {14}

For sample calculation, we used the data available in a previous study that also evaluated the outcomes of pain and anxiety related to administration of Influenza vaccine using or not the Buzzy® device [22]. For the outcome pain, we considered the mean values (± standard deviation) IG = 0.87 (± 0.07) and CG = 1.12 (±0.10). For the anxiety outcome, the values used for the basis of sample calculation were as follows: IG = 1.53 (± 0.13) and CG = 1.48 (± 0.15). The calculation was performed by the software G*power 3.1.9.2, adopting a statistical power of 90% and a significance level of 5%.

For the pain outcome, a sample of 86 participants was estimated in each group, for a total of 172 participants. For the anxiety outcome, a sample of 167 participants was estimated in each group, totaling 334 participants. In order to avoid losses, 350 participants will be selected and randomized to the control and intervention groups.

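### The pain sample size of 86 per group does not follow from the printed means and standard deviations, so the 90% power claimed for the primary outcome cannot be verified

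*Protocol article*

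**What the plan says.** All the figures are in the protocol article under Sample size {14}. The inputs come from one earlier study of the same device with influenza vaccine.

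- **Pain inputs:** "For the outcome pain, we considered the mean values (± standard deviation) IG = 0.87 (± 0.07) and CG = 1.12 (±0.10").
- **Anxiety inputs:** "IG = 1.53 (± 0.13) and CG = 1.48 (± 0.15"), under the same standard-deviation label.
- **Settings:** G*Power, 90% power, 5% significance. Sidedness is not stated.
- **Pain result:** "For the pain outcome, a sample of 86 participants was estimated in each group, for a total of 172 participants".
- **Anxiety result:** "For the anxiety outcome, a sample of 167 participants was estimated in each group, totaling 334 participants".
- **Enrolment:** "In order to avoid losses, 350 participants will be selected and randomized to the control and intervention groups".

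Trial design {8} fixes equal arms ("with allocation of participants in a 1:1 ratio"), so 350 means 175 per group. Outcomes {12} makes pain the primary outcome and describes this trial's measure: "Data collected from the numerical pain scale, from 0 to 10", with bands given in whole numbers. The between-group comparison is a t test or a Mann-Whitney test.

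**The concern.** A difference of 0.25 against a spread of 0.07 to 0.10 is an enormous standardised effect, and a handful of participants per arm would detect it. A requirement of 86 per arm cannot come from those inputs. Separately, a spread of a tenth of a point or less between individuals on a 0–10 pain scale is hard to believe.

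This is the power statement for the primary outcome, and the Discussion relies on the pre-calculated sample as a strength of the study. If neither the effect size nor the spread behind it can be traced, a reader cannot tell how large a pain difference the trial could detect, or how much weight a null result would bear.

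**Working it through.** **Method.** Two-sample t test, equal arms, two-sided 5%, exact noncentral t with 2n − 2 degrees of freedom and noncentrality d·√(n/2), where d is the difference divided by the pooled SD.

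**1. Anxiety, as a check on the method.** Difference 1.53 − 1.48 = 0.05. Pooled SD = √((0.13² + 0.15²)/2) = √0.0197 = 0.1404. d = 0.05/0.1404 = 0.356. Power is 0.899 at 166 per group and 0.901 at 167, so n = 167. The stated figure reproduces exactly with the printed ± values entered as SDs.

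**2. Pain, same method.** Difference 1.12 − 0.87 = 0.25. Pooled SD = √((0.07² + 0.10²)/2) = √0.00745 = 0.0863. d = 0.25/0.0863 = 2.90. Power is 0.755 at 3 per group and 0.923 at 4, so n = 4, against 86 stated. The following variants gave between 2 and 7 per group: one- or two-sided testing; the SD pooled, averaged or taken from either arm; alpha of 0.05, 0.025 or 0.01; and Mann-Whitney efficiency corrections.

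**3. What gives 86.** With d = 0.50, power is just under 0.900 at 85 per group and 0.903 at 86, so n = 86. For a 0.25-point difference, d = 0.50 means an SD of 0.25/0.50 = 0.50. Neither that d nor that SD appears in the article.

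**4. Are the printed pain SDs plausible?** A whole-number score whose mean has fractional part f has an SD of at least √(f(1 − f)).
- Mean 0.87: √(0.87 × 0.13) = 0.336, against 0.07 printed.
- Mean 1.12: √(0.12 × 0.88) = 0.325, against 0.10 printed.

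Even at these minima (pooled 0.331, d = 0.756) the requirement would be 38 per group, so they do not explain 86 either.

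**5. If the ± values were standard errors.** The person-level SD would be the printed value times the square root of the source study's arm size, which the article does not give. For assumed arm sizes:

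| Assumed source arm size | Pooled SD | n per group for 0.25 points at 90% |
|---|---|---|
| 50 | 0.61 | 127 |
| 100 | 0.86 | 252 |
| 200 | 1.22 | 502 |

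**6. Power for 0.25 points at the planned 175 per group.** The SDs are an assumed range, since the article gives no usable value.

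| Person-level SD | Power at 175 per group | n per group for 90% |
|---|---|---|
| 0.50 | 99.7% | 86 |
| 0.75 | 87% | 191 |
| 1.0 | 65% | 338 |
| 1.5 | 34% | 758 |
| 2.0 | 21% | 1346 |

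The 90% threshold at 175 per group falls at d = 0.347, that is, SD = 0.25/0.347 = 0.72. At 167 per group (334 evaluable) it falls at d = 0.356.

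**The case against.** The strongest reply is that 86 per group is not the operative number. Enrolment is 350, set by the larger anxiety requirement, so the pain calculation could be wrong without harming the trial. Taken literally, the printed pain inputs make even 86 far more than enough. The first part stands: power for pain should be judged at about 175 per group. It does not settle the matter, because the anxiety figure reproduces only by treating ± values of 0.13 and 0.15 as person-level SDs on a 0–10 scale, which is the same weakness.

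Three stronger readings are tempting, and the documents do not support them.

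- **That the trial is underpowered for pain.** The article gives no credible SD. At SD 0.50, the value that 86 per group implies for a 0.25-point difference, 175 per group has 99.7% power, and power stays at about 90% up to SD 0.72. Low power is a possibility that depends on an unknown SD.
- **That the printed SDs are impossible.** The lower bound of about 0.33 holds only for whole-number scores. Outcomes {12} describes this trial's scale. The source study's pain scale is not shown, and the article cites that study for an anxiety scale marked along a line. On a continuous line, 0.07 and 0.10 would be extremely implausible but not impossible.
- **That the ± values are standard errors.** They look like it, but the article does not confirm it. A misprint, or a different effect size entered in the software, is not excluded.

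**Conclusion.** The point holds as a calculation that cannot be reproduced and a power claim that cannot be verified. The printed pain inputs lead to 4 per group, not 86. That mismatch needs no assumption about standard errors or the source scale, and the exact reproduction of the anxiety figure rules out an unusual test or rounding as the explanation. This is not detail left to a fuller document: inputs, software, power, significance level and result are all printed and do not agree.

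That the SDs are implausibly small for individuals is a strong judgement for both outcomes; for pain it becomes a certainty only if the source scores were whole numbers. Whether 350 participants give 90% power for 0.25 points depends on a person-level SD of at most about 0.72, with all 175 per group analysed by a two-sided t test at 5%. Because this is the primary outcome's power statement and restating it is cheap, it should be corrected.

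**What to change.** In Sample size {14}, in this order:

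1. State the effect size actually entered in G*Power for pain, and whether the test was one- or two-sided.
2. Check the ± values for both pain and anxiety against the source study and label them for what they are. Only if they prove to be standard errors, convert them to person-level SDs using that study's arm sizes.
3. Remove or correct the 86 per group, and recheck the anxiety figure, since it sets the total.
4. Restate what the planned 350 delivers: 90% power at two-sided 5% for a standardised difference of about 0.35 (0.36 with 334 evaluable). Translate this into scale points with the verified SD, and give the resulting power for 0.25 points beside it.

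The cost is a look at the source study and a rewritten paragraph. Restating what 350 delivers requires no extra participants. The downside is that the stated power for a 0.25-point difference may become less favourable.
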